### Data Collection

Data will be collected at baseline and the end of the 8-week intervention period using self-reported questionnaires and qualitative interviews (refer to Table 3 for an overview).

In addition, to the items in Table 3, a qualitative researcher will conduct one-to-one in-depth interviews with all participants, their caregivers (if applicable), and health care providers involved in the delivery of SmartHeart. Interviews will be based on the UK National Institute for Health and Care Excellence (NICE) Evidence framework for digital health technologies [27] and will address acceptability, demand, practicality, frequency of monitoring, burden to participants, potential of provoking anxiety, scenarios in which the program would be best employed, compliance with functional components, facilitators, and barriers to participation.

**Table 3 table3:** Summary of outcome measures.

Items	Description or tool used to measure the item	Baseline	During intervention	Postintervention (8 weeks)
Recruitment and attrition	Study recruitment will be recorded by a trained research assistant and will include the total number of participants referred to the study, numbers who agree to participants, and those who enroll in SmartHeart. The research assistant will also record the number of participants that complete the study as a measure of attrition.	✓	✓	✓
Engagement	System use logs will be collected through the SmartHeart system and will provide data on the frequency of use of SmartHeart features. These will not require user input.	—^a^	✓	—
Weight	Withings Body Smart Bluetooth scales	✓	✓	—
Physical activity	Samsung Galaxy Watch Pro 5	—	✓	—
Heart rate	Samsung Galaxy Watch Pro 5	—	✓	—
Blood pressure	Withings blood pressure monitor Connect wireless blood pressure monitor	—	✓	—
Symptoms	Self-reported HF symptoms through the SmartHeart app	—	✓	—
Self-care	Self-Care of Heart Failure Index [28], version 6 [29]	✓	—	✓
Usability	System Usability Scale [30]	—	—	✓
Health-related quality of life	European Quality of Life 5D 5-level questionnaire [31]; Minnesota Living With Heart Failure Questionnaire [32]	✓	—	✓
Medication adherence	Philips Hue Infrared Motion Sensor (proxy); Medication Adherence Rating Scale [33]	✓	✓	✓
Hospitalization	Data provided by sites or study nurses.	—	✓	✓

^a^Not applicable.

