### SmartHeart Pilot Study Protocol

#### Objectives

This pilot study aims to assess the feasibility and acceptability of SmartHeart and inform the design of a larger hybrid RCT to assess effectiveness and implementation outcomes.

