#### Sample Size

The sample size for pilot feasibility studies should be based on practical considerations including participant flow, budgetary constraints, and the number of participants needed to reasonably evaluate feasibility goals [26]. For this study we aim to recruit a total of 20 participants, which will be sufficient to determine the feasibility of delivering SmartHeart, allowing for exploration of participant feedback regarding acceptability, usability, and uptake.

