### Self-Report Measures

Self-Care will be assessed using the Self-Care Heart Failure Index (SCHFI) [28], version 6 [29]. The SCHFI comprises 22 items and collects data on 3 domains (self-care maintenance, management, and confidence). Scores can be summed, but this is discouraged by the authors of the SCHFI. They recommend that the scales (maintenance, management, confidence) be used individually. Each scale is standardized to a score of 100. A score of ≥70 can be used as the cut-point to judge self-care adequacy, although evidence is provided that benefit occurs at even lower levels of self-care [29].** **The reliability and validity of this measure have been well documented [29].

The System Usability Scale (SUS) comprises 10 items (each question with a Likert scale ranging from strongly agree to strongly disagree) and was designed as a “quick and dirty” measure of the usability of either hardware or software or both by end users’ system [30]. Five questions are positively framed, and 5 questions are negatively framed. The process for computing an SUS score is as follows: (1) subtract 1 from the user’s Likert ratings for odd-numbered items or questions, (2) subtract the user’s Likert ratings from 5 for even-numbered items, (3) each item score will range from 0 to 4, and (4) sum the numbers and multiply the total by 2.5. This calculation will provide a range of possible SUS scores from 0 to 100.

Previous research has shown that a mean score of 68 is a useful benchmark [34].

Health-related quality of life will be measured using the European Quality of Life 5D 5-level (EQ-5D-5L) questionnaire [31] and the HF-specific Minnesota Living With Heart Failure Questionnaire (MLWHFQ) [32].

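### The System Usability Scale is scheduled only at 8 weeks, with no rating at earlier exit, so its mean may describe completers and overstate usability

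*Protocol article*

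**What the plan says.** On timing, the Data Collection section of the pilot protocol states: "Data will be collected at baseline and the end of the 8-week intervention period using self-reported questionnaires and qualitative interviews". In Table 3 the usability row names the SUS, with dashes under baseline and during the intervention and one tick under postintervention (8 weeks). Neither the text nor the table describes a rating at earlier exit.

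On how the score is read, Self-Report Measures gives the scoring rule ("This calculation will provide a range of possible SUS scores from 0 to 100") and then a reference value: "Previous research has shown that a mean score of 68 is a useful benchmark".

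On purpose, the Objectives section says: "This pilot study aims to assess the feasibility and acceptability of SmartHeart". The Sample Size section sets the target ("For this study we aim to recruit a total of 20 participants") and names usability among the things on which participant feedback will be explored.

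On losses, Table 3 says: "The research assistant will also record the number of participants that complete the study as a measure of attrition". Textbox 2 places attrition of up to 20% in green, above 20% to 35% in amber, and above 35% in red. Its four criteria are recruitment, engagement, self-care and attrition. The SUS is not among them.

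**The concern.** The SUS measures how easy the system is to use, and difficulty of use is a plausible reason for leaving. SmartHeart is installed at home and asks for daily weight, blood pressure and symptom entries. The protocol lists burden and barriers to participation among its interview topics, so the authors expect these to matter.

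If the only rating falls at week 8, a person who leaves the study at week 3 supplies no score. Should such people find the system harder to use than those who stay, the mean set beside 68 describes completers, not everyone who received SmartHeart. The eligibility criteria already exclude people judged likely to have difficulty using the system without support. Loss of the least satisfied users would be a second selection in the same direction.

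At stake is the pilot's only usability scale, and with it part of the information for redesign before the larger trial.

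**Working it through.** **The plan's own figure.** The SUS has 10 items, each scored 0 to 4 after recoding, and the sum is multiplied by 2.5. The minimum is 10 × 0 × 2.5 = 0 and the maximum is 10 × 4 × 2.5 = 100. The stated range is reproduced. The sample size has no power calculation to check: "The sample size for pilot feasibility studies should be based on practical considerations".

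**Inputs from the document.** N = 20 (Sample Size); benchmark 68 (Self-Report Measures); attrition limits of 20%, which is 0.20 × 20 = 4 people, and 35%, which is 0.35 × 20 = 7 people (Textbox 2).

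**Inputs assumed.** The document gives no SUS scores for people who leave, no reasons for leaving and no SUS standard deviation. I take a gap (completers' mean minus leavers' mean) of 0 to 40 points and a standard deviation of 12.5 to 20.

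**Formula.** With k leavers unrated among N, the mean over all N is the completers' mean minus (k/N) × gap. The bias of the completers' mean is therefore (k/N) × gap.

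| Assumed gap | Bias, 4 of 20 missing | Bias, 7 of 20 missing |
|---|---|---|
| 0 | 0 | 0 |
| 10 | 2 | 3.5 |
| 20 | 4 | 7 |
| 30 | 6 | 10.5 |
| 40 | 8 | 14 |

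For a 20-point gap, the completers' mean must reach 68 + 4 = 72 (4 missing) or 68 + 7 = 75 (7 missing) before the mean over all 20 is 68.

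**The same result as a break-even.** Suppose completers average 72 (an assumed value).

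- With 4 leavers, the mean over all 20 falls below 68 if the leavers would have averaged under (20 × 68 − 16 × 72)/4 = (1360 − 1152)/4 = 52. At 45, for example, it is (16 × 72 + 4 × 45)/20 = 66.6.
- With 7 leavers, the threshold is (1360 − 13 × 72)/7 = (1360 − 936)/7 = 60.6.

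**Scale against sampling error.** For 16 completers, the 95% half-width of the mean is 1.96 × 12.5/√16 = 6.1 points for a standard deviation of 12.5, and 1.96 × 20/√16 = 9.8 points for 20. At green-level attrition, a 4-point bias is smaller than the sampling error of the mean.

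**The case against.** The strongest case against has five parts.

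1. **It rests on silence.** Exit procedures are a detail that a journal article may leave to the full protocol. That is fair for exit procedures in general. But the SUS time point is stated in Table 3, and it is week 8 only. The point stands as a comment on that schedule. A reader might go further and infer that people who find the system too hard will never rate it. The document does not say this.

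2. **Stopping use is not leaving the study.** Engagement comes from system logs and attrition from study completion, and Textbox 2 treats them as separate criteria. Someone who gives up on the system but stays in the study is still due the SUS at week 8. This stands, and it limits the concern to people who leave the study itself.

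3. **Direction and size are assumed.** People with heart failure may also leave because of illness or hospitalization, and if leavers would score the same, the bias is 0. This stands. A reader might infer that the mean is biased upward; the document supports only that it may be.

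4. **No decision depends on it.** The SUS is outside the four progression criteria, 68 is a descriptive benchmark with no pass mark or test, and the analysis is descriptive. This stands, so it would be wrong to infer that the traffic-light outcome is affected.

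5. **Other data cover part of the gap.** Leavers count towards attrition, use logs need no user input, and interviews covering acceptability, burden and barriers are planned with all participants. This stands in part. None of these yields a SUS score, and the interviews share the end-of-intervention timing in the lead sentence.

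A single rating at the end of use is also a legitimate design. The weakness is only that nothing is scheduled for those who exit sooner.

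**Conclusion.** The concern holds in a limited, conditional form. As scheduled, a participant who leaves the study before week 8 contributes no SUS score. The mean may then describe completers and overstate usability against 68, provided that leaving is related to poor usability and that leavers are not rated in some way the article does not describe.

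Within the plan's own green and amber attrition limits, an assumed 20-point gap gives an overstatement of up to 4 points (20%) or 7 points (35%). With no gap it is 0. The document fixes neither the gap nor the reasons for leaving, so no single figure can be claimed.

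The consequence is confined to the reported usability result and to what is learned for redesign before the randomised trial. This is a minor improvement, worth making because it is cheap.

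**What to change.** In Table 3, change the usability timing to: SUS, together with the interview, at 8 weeks or at study withdrawal, whichever comes first. The form can be completed by phone or when loaned equipment is collected.

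Report three things: the number of participants with no SUS score, the mean over all rated participants who had SmartHeart installed, and the completers' mean alongside it.

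The cost is one 10-item form, and an earlier interview, for a handful of people: 4 at the green limit, 7 at the amber limit. The article reports 12 participants enrolled with recruitment still open, so on its own timeline the change could still be made for anyone who had not yet left.

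There are two drawbacks. Exposure will vary, since a rating after a short stay is not the same as one after 8 weeks, which is why both means should be shown. Some leavers will also decline, so the bias may shrink without vanishing. With a 20-point gap and 2 of 4 leavers rated (taking those two as typical of leavers), the mean of the 18 rated people lies 2 × 20/18 = 2.2 points below the completers' mean. The mean over all 20 lies 4 points below it, so about 4 − 2.2 = 1.8 points of bias remain. Reporting the number missing lets a reader judge this.

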### Self-Report Measures

Self-Care will be assessed using the Self-Care Heart Failure Index (SCHFI) [28], version 6 [29]. The SCHFI comprises 22 items and collects data on 3 domains (self-care maintenance, management, and confidence). Scores can be summed, but this is discouraged by the authors of the SCHFI. They recommend that the scales (maintenance, management, confidence) be used individually. Each scale is standardized to a score of 100. A score of ≥70 can be used as the cut-point to judge self-care adequacy, although evidence is provided that benefit occurs at even lower levels of self-care [29].** **The reliability and validity of this measure have been well documented [29].

The System Usability Scale (SUS) comprises 10 items (each question with a Likert scale ranging from strongly agree to strongly disagree) and was designed as a “quick and dirty” measure of the usability of either hardware or software or both by end users’ system [30]. Five questions are positively framed, and 5 questions are negatively framed. The process for computing an SUS score is as follows: (1) subtract 1 from the user’s Likert ratings for odd-numbered items or questions, (2) subtract the user’s Likert ratings from 5 for even-numbered items, (3) each item score will range from 0 to 4, and (4) sum the numbers and multiply the total by 2.5. This calculation will provide a range of possible SUS scores from 0 to 100.

Previous research has shown that a mean score of 68 is a useful benchmark [34].

Health-related quality of life will be measured using the European Quality of Life 5D 5-level (EQ-5D-5L) questionnaire [31] and the HF-specific Minnesota Living With Heart Failure Questionnaire (MLWHFQ) [32].

The EQ-5D-5L comprises 5Ds: mobility, self-care, usual activities, pain or discomfort, and anxiety or depression. Each dimension has 5 levels: no problems, slight problems, moderate problems, severe problems, and extreme problems. Participants are asked to indicate their health state by ticking the box next to the most appropriate statement in each of the 5Ds. This decision results in a 1-digit number that expresses the level selected for that dimension. The digits for the 5Ds can be combined into a 5-digit number that describes the patient’s health state. It also includes a visual analog scale that captures the participant’s self-rated health. This can be used as a quantitative measure of health outcomes that reflects the participant’s own judgment. The EQ-5D-5L has demonstrated excellent psychometric properties across a broad range of populations and health conditions [35].

The MLWHFQ is a 21-item multidimensional questionnaire designed to assess the health-related quality of life of people with HF in adults across physical, socioeconomic, and emotional or psychological dimensions. It is scored through a 6-point Likert scale (0-5), with a sum of item responses for total and dimension scores. The MLWHFQ has very good psychometric properties [36].

The Medication Adherence Rating Scale [33] is a 10‐item self‐report adherence scale that assesses both intentional (“I avoid using it if I can”) and nonintentional medication nonadherence (“I forget to use it”). Psychometric properties are well established [37]. Scores range from 0-10 with higher scores indicating better attitudes toward medication.

### Feasibility Outcomes

To inform decisions to progress to a definitive trial, there must be evidence of achieving key criteria for recruitment, engagement, self-care, and attrition. For this, the criteria in Textbox 2 will be used. These criteria were not based on published data but were developed following expert discussion with the chief investigator team, which comprised 2 cardiologists, an HF nurse specialist, 2 public health researchers, 2 exercise physiologists, one computer scientist, a health economist, and a biostatistician.

Feasibility criteria and metrics.Green: If all four green criteria are met, we will consider the study feasible (unless there is a clear indication from the qualitative interviews and our experience that would improve the study)At least 80% of the target sample size is recruited within 3 months.At least 50% of participants engaged with SmartHeart.At least 60% of participants maintained or improved their Self-Care of Heart Failure Index score.Attrition ≤20%. A rule of thumb states that >20% attrition poses threats to study validity [38].Amber: If one or more of our amber criteria are met, we will consider the study as likely feasible but will consider the results of the feedback from the qualitative interviews and our experience to improve whichever criteria are not at the “green light” level before considering a full trial.50%-79% of the target sample size is recruited within 3 months.35%-49% of participants engaged with SmartHeart.45%-59% of participants maintained or improved their Self-Care of Heart Failure Index score.Attrition 20.1%-35%.Red: If one or more red criteria are met, we would consider the study as likely not feasible with the current protocol.<50% of the target sample size is recruited within 3 months.<35% of participants engaged with SmartHeart.<45% of participants maintained or improved their Self-Care of Heart Failure Index score.Attrition >35%.

### Analysis

Descriptive statistics (mean and SD for continuous data, N and percentage for categorical) will be presented for all quantitative primary and secondary (eg, self-care behaviors, Health-Related Quality of Life) outcomes and will be the primary form of analysis. The EQ-5D-5L questionnaire will be scored using the Australian value set [39]. Within a person, cross-correlation matrices will also be generated [40].

Interviews will be audio-recorded and transcribed. We will use framework analysis to analyze the interviews, using predefined categories according to the NICE Evidence framework for digital health technologies [27].

### Ethical Considerations

The study received ethical approval from the Deakin University Human Research Ethics Committee (HREC/76317/MH-202). A participant information sheet and consent form will be sent to participants during the baseline assessment. Written informed consent will be obtained at the baseline assessment before data collection.

## Results

The SmartHeart project, including the proposed pilot study, received funding from the National Health and Medical and Research Council grant (grant number 2018698) and commenced in January 2021. This study was conducted in collaboration with health and academic partners in the states of Victoria and Queensland, Australia. Recruitment for the pilot trial started in August 2024 and will be completed by March 2025. We have currently enrolled 12 participants. Follow-up of all participants will be completed by the end of May 2025. Once analysis from the pilot study has been completed, we will submit the findings for publication.

## Discussion

### Principal Findings

This article reports on the formative development of the SmartHeart system, a smart health ecosystem with advanced telemonitoring and behavioral support, offering a comprehensive, integrated, and coordinated approach to HF management. We also outline a protocol for piloting SmartHeart to inform a future RCT.

Consistent with the need to integrate consumers in health research [41], we have undertaken extensive user-centered design and engagement with end users. A comprehensive program of research, following the IDEAS framework was used in developing SmartHeart. Reflecting on the design and development process, we benefited greatly from using the IDEAS framework. Our formative work involving a scoping review, stakeholder interviews, and a Delphi survey was important for ideation and informing the prototype features and functions. Co-design workshops were critical in identifying the needs of users and health care providers. We hypothesize that this will likely maximize the acceptability, engagement, and usability of the SmartHeart system. However, the downside to this co-design approach was the much longer development timeframes to achieve the SmartHeart prototype.

SmartHeart incorporates a conversational agent (Amazon Alexa). With ongoing development, conversational agents have evolved into digital systems that aid the delivery of health interventions for individuals at the places most convenient for them. Using voice to interact with these agents is a more natural user interface than traditional mouse, keyboard, or touch interfaces, which may lower barriers to entry for many people, especially older adults, those culturally and linguistically diverse, and people with low literacy [42]. We also provide access to SmartHeart in multiple languages, increasing the accessibility of support to those who speak languages other than English. Furthermore, in Australia, SmartHeart could have a significant impact by providing greater access to health care, especially in high-priority rural and regional areas.

There are some limitations of the current system that warrant consideration. First, the system is currently Android-based; however, we offer participants an Android phone for the duration of the study, and we are developing an iOS version for future use. Second, the Samsung Galaxy watch used to collect data from participants is also only compatible with the Android system. Our future plans are to support most off-the-shelf smartwatches in the market, including Fitbit (Google; iOS and Android), Apple Watch (iOS), and Garmin. Third and finally, we use a cloud-to-cloud approach, which can be problematic when third-party providers (eg, Withings) provide updates affecting data capture. Our team will check and maintain the system on a regular basis to ensure all components are up to date, helping to mitigate this issue.

A risk mitigation strategy plan was developed for the funding application that supported this project. A key risk is the slow recruitment of participants. Our current recruitment strategy includes recruitment from participating partner hospital sites; however, we will mitigate risk by also recruiting from community HF support groups, general practices, and online through social media. The small number of participants may also be a risk as this may not be sufficient to inform feasibility; however, we have indicated in our ethics application that we may extend recruitment to mitigate this risk. Data security is another risk, which will be addressed by ensuring all data are anonymized, and data storage meets Melbourne and Deakin’s Research Conduct Policy and the Research Data and Primary Materials Management Procedure. As mentioned earlier, all data will be stored securely on password-protected servers and in accordance with ethical procedures. Finally, because participants are required to provide consent in English, it is possible that the benefit of SmartHeart being available in different languages will not be realized. The requirement for consent in English is based on logistics; we do not have a resource to pay for interpreters; however, most participants in Australia for whom English is not a first language can read English for consent purposes.

The SmartHeart system has significant potential for future expansion and enhancement. While our current prototype uses desktop smart speakers, the integration of conversational agents on mobile devices (eg, phones, tablets, smartwatches) could extend the system’s reach beyond the home environment. Furthermore, we are exploring the integration of generative artificial intelligence to enhance user engagement through more natural dialogue and personalized responses, leveraging a curated guideline-based database and retrieved augmented generation techniques. While the project’s initial focus targets people living with HF, the system’s architecture supports broad applicability to other long-term conditions. This versatility will be particularly beneficial for the increasing number of people managing more than one long-term condition. The system's adaptability is enhanced by the fact that challenges associated with HF significantly overlap with other health conditions, such as other cardiovascular conditions, chronic obstructive pulmonary disease, and diabetes, making the core functionality transferable. Potential adaptations include customizing symptom questionnaires for one or more conditions, implementing different wireless sensors, and refining the algorithms and support messages.

The next step is to assess the feasibility of this version of the SmartHeart system with both people with HF and health care providers. A pilot study will provide valuable information on feasibility and preliminary effects, which will inform the design of a larger proposed RCT. If clinical and cost-effectiveness are subsequently demonstrated, SmartHeart could augment existing health care services to support people with HF to stay well living in the community and living independently. The primary benefit of this solution is to empower people with HF to be more actively engaged in self-care and realize the unfulfilled potential for digital health to transform health care delivery. If proven feasible, it could improve clinical outcomes (hospital admissions, self-care, health-related quality of life) and reduce the cost burden of the health care system. The SmartHeart concept aligns with recent calls for a health care shift from clinics to the home, with digital health support [6] and a recent European Society of Cardiology position statement [43] to address key elements of digital health implementation.

